**7.4. CRITERIA FOR EARLY WITHDRAWAL**

Participants may be withdrawn from trial treatment if they are intolerant to the therapeutic product, experience toxicity related side-effects or inter-current illness necessitating cessation of the therapy at any time throughout the trial at the physician's discretion.

Subjects may withdraw consent for any reason at any time without prejudice to their normal care. Patients withdrawing from the study will continue to be monitored and managed within their routine clinic by their named consultant.

Withdrawn trial subjects will not be replaced. Withdrawal of consent may be regarded as a withdrawal from trial medication or any other components which form part of the Informed Consent Form signed by the participant.

At the time of withdrawal, a full efficacy and safety evaluation should be performed if patient consents. Treatment cessation and reason for discontinuation should be documented on the applicable CRF and medical records.

**8. STUDY PROCEDURES****8.1 INFORMED CONSENT PROCEDURES**

Written informed consent will be obtained from each patient by the Principal Investigator or designee. Informed consent will be prepared according to NRES and study sponsor requirements for informed consents.

Patients who are candidates for the study will receive a Patient Information Sheet (PIS) which explains the purpose of the trial and highlights the benefits and risks of participation in the trial. Patients must be given adequate time (minimum 24 hours) to review the information and must have the opportunity to ask the Principal Investigator or designee any questions relating to the trial. Following this, the patient must sign an informed Consent Form (CF) in the presence of the Principal Investigator or designee who must then countersign the CF.

Written consent must be obtained prior to any study-specific procedures being performed, including any study specific screening procedures prior to randomisation. At the time of consent, participants must be informed that they have the right to withdraw their participation in the trial at any stage and that doing so will not prejudice their future clinical management and care.

## **8.2.SCREENING (VISIT 1)**

Visit schedule screening will entail evaluation of:

- Inclusion and exclusion criteria
- Demographic data including age, gender and medical history
- Characteristics of PR
  - o Number of joint attacks (per month)
  - o Intensity of attack (analogue scale 0-10 cm)
  - o Presence of inflammation during attacks (swelling, eritema)
- Clinical examination
- Concomitant drugs
- Joint assesment
- Routine blood test ( include at least CRP, ESR Hb, WBC, platelets, cholesterol, ALT/AST, creatinine)
- Rheumatoid Factor
- Anti-CCP.

Hand and feet radiographs (: unless an X-ray was performed < 6 months)

-

## **8.3 BASELINE VISIT (VISIT NUMBER 2) AND FOLLOW-UP**

- Clinical examination

- Concomitant drugs

Joint assement

Randomisation

ACR/EULAR criteria for RA

Specific blood tests ( include determination of serum ACPA ans anti-CarP)

Autoantibodies

Adverse events

#### **8.4 VISIT NUMBERS (VISIT 3)**

- Clinical examination

- Concomitant drugs

Joint assement

ACR/EULAR criteria for RA

Specific blood tests ( include determination of serum ACPA ans anti-CarP)

Autoantibodies

Adverse events

#### **8.5 VISITS NUMBERS (VISIT 4, 8, AND EARLY WITHDRAWAL/STOP TREATMENT)**

- Clinical examination

- Concomitant drugs

Joint assement

ACR/EULAR criteria for RA

Routine blood tests

Adverse events

Specific blood tests ( include determination of serum ACPA and anti-CarP)( in  
Early withdrawal /stop treatment visits)

#### **8.6 VISITS NUMBERS (VISIT5,7, 9)**

- Clinical examination
- Concomitant drugs

Joint assessment

ACR/EULAR criteria for RA

Adverse events

#### **8.7 VISITS NUMBERS (VISIT6 AND 10)**

- Clinical examination
- Concomitant drugs

Joint assessment

ACR/EULAR criteria for RA

Routine blood test

Specific blood tests

Adverse Events

**8.8 STUDY VISIT SCHEDULE**

| Visit number                 | 1 | 2 | 3 | 4 | 5 | 6  | 7  | 8  | 9  | 10 | Treatment cessation/early withdrawal |
|------------------------------|---|---|---|---|---|----|----|----|----|----|--------------------------------------|
| Timeline (months)            |   | 0 | 3 | 6 | 9 | 12 | 15 | 18 | 21 | 24 |                                      |
| Informed Consent             | x |   |   |   |   |    |    |    |    |    |                                      |
| Inclusion/Exclusion criteria | x |   |   |   |   |    |    |    |    |    |                                      |
| Demographics                 | x |   |   |   |   |    |    |    |    |    |                                      |
| Medical history              | x |   |   |   |   |    |    |    |    |    |                                      |
| Concomitant drugs            | x | x | x | x | x | x  | x  | x  | x  | x  | x                                    |
| Clinical exam                | x | x | x | x | x | x  | x  | x  | x  | x  | x                                    |
| Joint assessment             | x | x | x | x | x | x  | x  | x  | x  | x  | x                                    |
| Routine blood test           | x |   |   | x |   | x  |    | x  |    | x  | x                                    |
| Hand/feet X-ray*             | x |   |   |   |   |    |    |    |    |    |                                      |
| Randomisation                |   | x |   |   |   |    |    |    |    |    |                                      |
| ACR/EULAR criteria for RA    | x | x | x | x | x | x  | x  | x  | x  | x  | x                                    |
|                              |   |   |   |   |   |    |    |    |    |    |                                      |
| Specific blood tests**       |   | x | x |   |   | x  |    |    |    | x  | x                                    |
| Adverse events               |   | x | x | x | x | x  | x  | x  | x  | x  | x                                    |

RF: rheumatoid factor CCP: cyclic citrullinated peptide.

Routine blood test include at least CRP, ESR Hb, WBC, platelets, cholesterol, ALT/AST creatinine

\*: unless an X-ray was performed < 6 months

\*\* : specific blood test include the determination of serum ACPA and anti-CarP autoantibodies

**All** patients included after the screening will be followed until month 24. Visits will be performed every three months according to standard clinical practice. In each visits the achievement of the RA classification criteria will be analysed. The

frequency, duration and intensity (in a visual analogue scale) of the joint attacks will be analysed together with the presence of joint swelling or erythema.

Concomitant therapy will be recorded . Systemic steroids (oral or parenteral) in an equivalent dose higher than 7.5 mg/day of prednisone are not permitted during the study.

## **8.9 END OF STUDY TRIAL DEFINITION**

The end of the study trial will be triggered 6 months after the last recruited patient completed final study visit (Last Patient Last Visit LPLV). This additional months will allow to monitoring and statistical analysis .

Those patients who achieve the classification criteria of RA at any time during the 24 month of the trial are considered non responders and will discontinued the study protocol and treated according to physician criteria.

Whenever possible, patients will be followed by entering their data in the CRd until the end of 10 visits

## **9.STATISTICAL ANALYSIS:**

### ***General Remarks***

The statistical analysis will be carried out in accordance with the principles specified in the International Conference on Harmonization (ICH) Topic E9 (CPMP / ICH / 363/96). A detailed Statistical Analysis Plan (SAP) agreed upon before the data base closure and the break of the randomisation codes. This SAP will follow the general regulatory recommendations given in the ICHE9 guidance, as well as other specific

---

 CPMP/ICH/363/96. ICH E9 Statistical Principles for Clinical Trials. URL:  
[http://www.ema.europa.eu/ema/pages/includes/document/open\\_document.jsp?webContentId=WC500002928](http://www.ema.europa.eu/ema/pages/includes/document/open_document.jsp?webContentId=WC500002928), last access: 30-Oct-2017.

 CPMP/ICH/363/96. ICH E9 Statistical Principles for Clinical Trials. URL:  
[http://www.ema.europa.eu/ema/pages/includes/document/open\\_document.jsp?webContentId=WC500002928](http://www.ema.europa.eu/ema/pages/includes/document/open_document.jsp?webContentId=WC500002928), last access: 30-Oct-2017.

guidance on methodological and statistical issues. Also, it will stick to the recommendations given by the consensus documents of the scientific journals to improve reliability and value of medical research literature by promoting transparent and accurate reporting of clinical research studies.

The SAS System^6 (Release 9.4, or an upgraded version), or equivalent validated statistical software, will be the statistical software used to analyse the data sets.

A summary of the overall approach to statistical analysis is presented hereafter.

### ***Sample size calculation***

The sample size will be calculated according to the primary endpoint, (progression to RA at 24 months). In the primary analysis, we will report the primary endpoint in each group which will be compared using the Fisher's exact test.

Previous studies found a 2-year progression rate of approximately 40-50%. Assuming a 2-year progression rate of at least 42% in the control group according to previous data and 11% in the experimental group, a sample size of 35 patients per group (total 70) will be needed to reach a power of 80% at a nominal level of a two-sided alpha of 0.05, according to nQuery validated software

The study will be performed in 20 sites (Rheumatology Services or Units) from hospitals) with a median recruitment of 5 patients per centre. The study enrolment period will be 41 months

- 
- 3 EMEA Scientific Guidelines for Human Medicinal Products, Clinical Efficacy and Safety Guidelines, General Guidelines. URL: [http://www.ema.europa.eu/ema/index.jsp?curl=pages/regulation/general/general\\_content\\_000602.jsp&mid=WC0b01ac05807d91a4](http://www.ema.europa.eu/ema/index.jsp?curl=pages/regulation/general/general_content_000602.jsp&mid=WC0b01ac05807d91a4), last access: 30-Oct-2017.
  - 5 EQUATOR-network (Enhancing the Quality and Transparency of Health Research). URL: <http://www.equator-network.org/resource-centre/library-of-health-research-reporting/>, last access 09-Dec-2016
  - 6 SAS version 9.4 software, SAS Institute Inc., Cary, NC, URL: <http://www.sas.com/>, last access, 30-Oct-2017.
  - 7 Elashoff JD. nQuery Version 7.0 Advisor User's Guide. Statistical Solutions Ltd, Los Angeles, CA 2007.
  - 8 Fleiss, J.L. Statistical Methods for Rates and Proportions. 2nd Edition John Wiley & Sons Inc., New York (1981) pp. 24-26
  - 10 R.G. Thomas and M. Conlon "Sample size determination based on Fisher's exact test for use in 2 x 2 comparative trials with low event rates" Controlled Clinical Trials 13(1992) pp. 134-147

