## **5. INTRODUCTION**

### **5.1 BACKGROUND:**

Palindromic rheumatism (PR) is a clinical entity characterized by intermittent arthritis lasting a few days that tends to recur and, in up to 50-60% of patients, progresses to rheumatoid arthritis (RA)(1). Approximately 15% of RA patients initially had PR (2). This high risk of RA progression is observed during the first years of evolution of PR (3). Several prognostic factors for RA in these patients have been identified, such as gender (female), involvement of the small joints of the hands, and serum autoantibodies such as rheumatoid factor (RF) or anticitrullinated peptide antibodies (ACPA)(4-5). After our first description of the high prevalence of ACPA in PR (6), this association has been confirmed in different populations (5,7,8). ACPA have been described as a biomarker of RA progression in RP patients (5), although a significant proportion of ACPA+ PR patients, even when titres are high, do not develop RA in the long term (9). Why some patients with PR progress to RA and others do not is unclear. Recently, our group demonstrated that the ACPA repertoire is restricted, with less citrullinated peptide specificities and less isotype usage than found in established RA (10), as occurs in the preclinical phase of RA (11) or in family members of patients with RA (12). It is unclear whether PR patients with a less restricted ACPA repertoire in the early phases of the disease are less prone to progress to RA.

There is no specific treatment for PR that prevents progression to persistent arthritis or RA. Gold salts and antimalarial drugs have shown efficacy in clinical symptoms, with a lower frequency of attacks, and even remission, in patients with PR treated with these antirheumatic drugs (1,13). Most rheumatologists use antimalarials (hydroxychloroquine) as the first option to treat PR. No studies have been made using

methotrexate, leflunomide or sulfasalazine (1). In a Canadian study, antimalarials increased the time to progression to RA in patients with PR (14).

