#### **6.4 STUDY SCHEME DIAGRAM**

### **7. SUBJECT SELECTION**

#### **7.1 NUMBER OF SUBJECTS.**

70 patients with Palindromic Rheumatism criteria of Guerne- Weisman (35 treated with abatacept and 35 with hydroxychloroquine)

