#### ***Procedures to account for missing or spurious data***

The handling of missing data will follow the principles specified in the ICH-E9 and the CPMP/EWP/1776/99 Rev1. Guideline on Missing Data in confirmatory trials Guidelines. Patients with missing data for the primary outcome will be considered as failures irrespectively to the drop-out reason. A detailed more detailed description will be included in the SAP.

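### The 80% power assumes that every primary outcome is observed; at the planning rates it falls below 80% once losses are similar in both arms and scored as failures

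*Protocol*

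**What the plan says.** All references are to the protocol.

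- **Section 9, Sample size calculation.** The two groups' progression proportions are the primary endpoint, "which will be compared using the Fisher's exact test". The inputs are "Assuming a 2-year progression rate of at least 42% in the control group according to previous data and 11% in the experimental group", "at a nominal level of a two-sided alpha of 0.05". The result is that "a sample size of 35 patients per group (total 70) will be needed to reach a power of 80" per cent. The paragraph also cites earlier studies with 2-year progression of roughly 40-50%. It mentions no loss to follow-up.
- **Section 7.1.** Planned enrolment equals the calculated number: "35 treated with abatacept and 35 with hydroxychloroquine".
- **Section 7.4.** "Withdrawn trial subjects will not be replaced". The same section asks for a full evaluation at withdrawal if the patient agrees.
- **Section 9, Procedures to account for missing or spurious data.** "Patients with missing data for the primary outcome will be considered as failures irrespectively to the drop-out reason". Further detail is deferred to the SAP.
- **Section 9, Analysis populations.** The primary set is every randomised patient who received study treatment, apart from narrowly defined eligibility exclusions. A treated patient with no outcome therefore stays in the denominator.
- **Sections 8.8 and 8.9.** RA criteria are assessed at the treatment cessation/early withdrawal visit, and data entry continues to the tenth visit where possible.

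**The concern.** The sample size paragraph and the missing-data rule belong to the same section but do not meet. Thirty-five per arm is the bare requirement for 42% versus 11% with complete data. Once a patient's outcome is missing, the plan neither replaces the patient nor drops the patient from the analysis; it adds a failure to that patient's arm. Equal losses then raise both failure rates and narrow the gap between them, which costs more power than losing the patients outright.

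The 80% is what a reader will use to interpret a non-significant result. If the planned analysis has appreciably less power, such a result would be given more weight against abatacept than it deserves.

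**Working it through.** **Inputs from the protocol.** n = 35 per arm; control rate 0.42; abatacept rate 0.11; two-sided alpha 0.05; Fisher's exact test; missing primary outcome = failure; no replacement.

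**Assumed input.** The proportion d of patients with a missing primary outcome. The protocol gives none, so a range is shown. Loss is taken as unrelated to progression and, unless stated otherwise, equal in both arms.

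**Step 1: reproduce the stated figure.** Enumerate all 36 × 36 pairs of event counts, mark those with Fisher p ≤ 0.05, and sum their binomial probabilities:

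Power = Σ Bin(x; 35, p₁) · Bin(y; 35, p₂) · 1[Fisher p(x, y) ≤ 0.05]

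With p₁ = 0.42 and p₂ = 0.11 this gives 79.6%; 36 per arm gives 81.1%. The protocol's 80% is reproduced with every outcome observed, and there is no margin.

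**Step 2: apply the missing-data rule.** A patient is a failure if lost, or if retained and progressing:

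p′ = d + (1 − d)p

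At d = 0.10:
- control: 0.10 + 0.90 × 0.42 = 0.478
- abatacept: 0.10 + 0.90 × 0.11 = 0.199

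The difference shrinks from 31 to 27.9 percentage points. With n still 35 per arm:

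| Equal loss d | Control p′ | Abatacept p′ | Exact Fisher power |
|---|---|---|---|
| 0% | 42.0% | 11.0% | 79.6% |
| 2% | 43.2% | 12.8% | 75.9% |
| 5% | 44.9% | 15.5% | 70.7% |
| 10% | 47.8% | 19.9% | 62.7% |
| 15% | 50.7% | 24.4% | 54.7% |
| 20% | 53.6% | 28.8% | 46.5% |

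**Step 3: separate the two causes at 10% loss.** Simply excluding lost patients leaves 35 × 0.9 = 31.5 per arm. Power is 74.2% at 31 and 76.2% at 32, a fall of about 3 to 5 points. Scoring them as failures costs 79.6 − 62.7 = 16.9 points. Most of the fall comes from the scoring rule.

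**Step 4: vary the control rate over the protocol's own range (abatacept 11%).**

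| Control rate | No loss | 10% equal loss, missing = failure |
|---|---|---|
| 40% | 74.3% | 56.7% |
| 42% | 79.6% | 62.7% |
| 45% | 86.2% | 71.1% |
| 50% | 93.7% | 82.5% |

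**Step 5: unequal loss at 42% versus 11%.**
- Control 5%, abatacept 10%: 52.9%.
- Control 10%, abatacept 5%: 78.8%.
- Control 15%, abatacept 5%: 85.5%. This gain is spurious: extra control losses are counted as control failures, which biases the comparison towards abatacept.

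**The case against.** **The stated figure is not a miscalculation.** This is right. The 80% is correct for its inputs; what is absent is the condition of complete outcomes.

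**The loss rate is the reviewer's.** This also stands. The protocol gives no rate, so no single row of the table is a prediction. Moreover, only a missing primary outcome matters. Stopping treatment is different, and Sections 7.4, 8.8 and 8.9 provide for an evaluation at withdrawal and continued follow-up where possible. Those provisions should reduce missing outcomes, but they are not an allowance in the sample size. Even 2% loss, under one patient per arm, takes about 4 points.

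**The control rate may exceed 42%.** It may. At 50%, power is still 82.5% with 10% loss. A reader might infer that 80% is attainable only if nobody is lost, or that true power is about 63%. Neither follows: the first holds only at 42% versus 11% with similar loss in both arms, and the second is one assumed scenario.

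**Readings that the documents do not support.** Section 5.1 reports that "antimalarials increased the time to progression to RA in patients with PR", from which a reader might infer that 42% is too high for a hydroxychloroquine arm and test rates of 30% or 35%. The protocol does not say whether the data behind 42% came from treated or untreated patients, and those rates lie outside its planning range. Nor does describing 42% as a minimum contradict a range given only approximately as 40-50%; that is loose wording.

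**The SAP may settle it.** It may refine missing-data handling, but the sample size, non-replacement and missing-as-failure rules are already fixed in the protocol. The stated power fits the planned analysis under loss only if the rule or the figure changes.

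**Conclusion.** The point holds in a limited form and should be fixed. The protocol's 80% is the power of a Fisher test on 70 fully observed outcomes (79.6% exact), not of its primary analysis once outcomes are missing. At 42% versus 11%, with equal loss unrelated to outcome, power falls to 70.7% at 5%, 62.7% at 10% and 46.5% at 20%. In the 10% case, a true 31-point effect would be missed in 37.3% of trials, rather than the roughly one in five that the protocol implies.

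The size depends on three things that the protocol does not fix: the loss rate, its balance between arms, and where the control rate falls between 40% and 50%. Over that range power is 74.3% to 93.7% with no loss and 56.7% to 82.5% at 10% loss. This is an omitted assumption that affects how the result will be read. It does not show that the trial is too small to run.

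**What to change.** In Section 9, Sample size calculation, replace the single figure with a conditional statement such as:

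> With 35 patients per group, power is about 80% if all primary outcomes are observed and the progression rates are 42% and 11%. If missing outcomes are counted as failures and loss is equal in both groups, power is about 71%, 63% and 46% at 5%, 10% and 20% loss.

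Add the power for control rates from 40% to 50%, with no loss and at 10% loss, from the Step 4 table. State the loss rate that the sponsor expects and its basis. If the missing-data rule is changed, quote power for the analysis that replaces it, since that rule causes most of the fall.

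The cost is one paragraph. No extra patients, visits or changes to the endpoint or test are required. The drawback is a less favourable stated power.

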***Analysis populations***

There will be the following analysis populations for this study:

- 1) Modified Full Analysis Set (mFAS): All patients who are randomized into the study and who have received the investigational product (any of the 2 arms treatment) will be included in the mFAS population. The accepted exclusions, as per the ICHE9, are predefined as follows:

- Participants who fail to satisfy an entry criterion may be excluded from the analysis without the possibility of introducing bias only under the following circumstances:

- i) The entry criterion was measured prior to randomization;
- ii) The detection of the relevant eligibility violations can be made completely objectively;
- iii) All participants receive equal scrutiny for eligibility violations;
- iv) All detected violations of the particular entry criterion are excluded.

- 2) Per Protocol Population: Per protocol (PP) patient sets will be defined as those patients included in the mFAS set without major protocol deviations that might impact the study's main assessments. These deviations will be assessed during the data review prior to database lock.

- 3) The Safety population is defined as all randomized participants who received the investigational product (any of the two arm treatment). In this study the Safety population will have the same definition than the mFAS subset and thus, all safety analysis will be conducted on the mFAS population.

The primary analysis set for the main analyses will follow the ‘*ICH Topic E9 - Statistical Principles for Clinical Trials*’ (CPMP/ICH/363/96)‘ and will be based on the modified full analysis set (i.e. ITT or mFAS; see beginning of section 0, above).

However, the main outcome will be also analysed using the PP set for sensitivity purposes.

The precise reasons for excluding participants from each population will be fully defined and documented independently of the randomization codes during the data blinder review and before data lock.

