| SHORT TITLE                       | PALABA                                                                                                                                                                                                                                                                                                                                                                                                                                                                                                                                                                                                         |
| PROTOCOL VERSION/DATE             | Protocol V2.0. date 22-12-2020                                                                                                                                                                                                                                                                                                                                                                                                                                                                                                                                                                                 |
| METHODOLOGY                       | Type of study: multicenter open-label randomized controlled clinical trial                                                                                                                                                                                                                                                                                                                                                                                                                                                                                                                                     |

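### In this open-label trial the primary set is treated-only yet is labelled ITT, and no analysis of all randomised patients is planned

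*Protocol*

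**What the plan says.** The synopsis describes the design as "Type of study: multicenter open-label randomized controlled clinical trial".

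Section 9, Analysis populations, defines three sets.

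- **mFAS:** "All patients who are randomized into the study and who have received the investigational product (any of the 2 arms treatment) will be included". Entry violations may also be removed, under four listed conditions.
- **Per protocol:** mFAS patients without major deviations, used as a sensitivity set for the main outcome.
- **Safety:** the same definition as the mFAS.

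The main analysis "will be based on the modified full analysis set (i.e. ITT or mFAS", so the treated-only set is given as another name for ITT. Reasons for exclusion are to be "documented independently of the randomization codes during the data blinder review and before data lock". Under General Remarks, the SAP is to be "agreed upon before the data base closure and the break of the randomisation codes".

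Other parts of the protocol bear on this.

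- Section 9 on missing data counts a missing primary outcome as a failure whatever the reason for drop-out.
- Section 5.2 has abatacept shipped to hospital pharmacies by a logistics company, and hydroxychloroquine obtained through usual care with traceability left to the researchers.
- Section 8.8 has everyone included after screening followed to month 24. Section 8.9 qualifies this to whenever possible.

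**The concern.** Leaving out patients who never start is usually defended on the ground that the decision not to start cannot depend on the arm. Masking supplies that ground, and this trial has none. Patient and investigator can know the arm before the first dose, and the arms differ in route of administration and in supply. Not starting can therefore depend on allocation, and those who do not start may differ in their risk of RA.

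The missing-data rule adds to this. A patient who starts and is lost counts as a failure, while a patient who never starts and is lost disappears from both numerator and denominator. If non-starting differs between arms, the two arms are in effect treated differently.

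No planned analysis would show the effect. The per-protocol set lies inside the mFAS, so comparing the two reveals nothing about patients outside both. The ITT label also invites a reader to believe that an all-randomised analysis has been done.

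**Working it through.** **Inputs (Protocol section 9).** 35 patients per arm; progression 42% on control and 11% on abatacept; two-sided alpha 0.05; Fisher's exact test; missing outcome = failure. The number of non-starters is not given, so 1 to 3 in one arm is assumed.

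**Step 1: the plan's own figure.** Exact power is the sum of Bin(x; n, 0.42) × Bin(y; n, 0.11) over all tables (x, y) with Fisher p ≤ 0.05. At n = 35 per arm it is 79.6%, and at n = 36 it is 81.1%. The stated 35 per arm for 80% is reproduced to rounding. It refers to 35 analysed per arm.

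**Step 2: two abatacept non-starters.** Take control 15/35 = 42.9%, close to the assumed 42%, and 5 abatacept events among those who started.

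| Handling of the two non-starters | Abatacept | Difference from control | Fisher p |
|---|---|---|---|
| Dropped (mFAS) | 5/33 = 15.2% | 27.7 points | 0.017 |
| Kept, outcome missing, counted as failures | 7/35 = 20.0% | 22.9 points | 0.070 |
| Kept, followed and free of RA | 5/35 = 14.3% | 28.6 points | 0.016 |

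The set decides significance when the outcomes are missing. It hardly matters when the patients are followed and remain free of RA.

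**Step 3: other counts against control 15/35, outcomes missing.**

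| Abatacept events | Non-starters | Dropped | Kept as failures |
|---|---|---|---|
| 6 | 1 | 6/34, p = 0.036 | 7/35, p = 0.070 |
| 4 | 1 | 4/34, p = 0.006 | 5/35, p = 0.016 |
| 4 | 2 | 4/33, p = 0.007 | 6/35, p = 0.036 |
| 4 | 3 | 4/32, p = 0.007 | 7/35, p = 0.070 |

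At about the design rates (15/35 v 4/35, p = 0.006) the conclusion survives one or two such patients. It fails at three, all in the abatacept arm and all unobserved.

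**Step 4: non-starters in the control arm.** Around 15/35 v 4/35, dropping three RA-free controls gives 15/32 v 4/35, p = 0.002, so the conclusion is unchanged. Around a borderline 13/35 v 5/35 (p = 0.054), dropping three RA-free controls gives 13/32 v 5/35, p = 0.026. If three control non-starters were unobserved and kept as failures, the comparison would be 16/35 v 5/35, p = 0.008, and dropping them (p = 0.026) would then work against abatacept. The direction is not fixed.

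**The case against.** Non-starters may be few. Randomisation takes place at the baseline visit (sections 8.3 and 8.8), and patients with a contraindication or intolerance to either drug are already excluded (section 7.3). This stands, and it limits the claim: the protocol gives no basis for saying that the randomised comparison is lost, only that it is not guaranteed.

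A reader might also infer more than the text supports on four points.

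- **That dropping a few controls manufactures significance.** Much of the swing from 13/35 v 5/35 comes from the discreteness of Fisher's test. One dropped patient (13/34 v 5/35) already gives p = 0.030, while equal arms of 34 (13/34 v 5/34) give p = 0.053. The example also needs the dropped patients to have been followed and found free of RA.
- **That eligibility exclusions are open-ended.** They are not: "Participants who fail to satisfy an entry criterion may be excluded from the analysis without the possibility of introducing bias only under the following circumstances", followed by four conditions, one of which is "The detection of the relevant eligibility violations can be made completely objectively". If these are met, this route adds little bias.
- **That an arm-unaware data review is impossible.** Data reviewers and statisticians can be kept from the allocation in an open-label trial. What fails is the milestone: with allocation known at sites, the breaking of codes marks no point before which knowledge of the arm is absent.
- **That a list of major deviations is missing.** That belongs in the SAP, which is not shown.

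The 12-month interim evaluation in section 9 mentions p-values, which suggests a comparison by arm. The protocol does not say who sees it or whether it comes before the SAP.

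**Conclusion.** The point holds in a limited form. The protocol itself, not a detail left to the SAP, fixes a treated-only primary set in an open-label trial, gives it the name ITT, and plans no analysis of all randomised patients. Non-starting that depends on allocation would go uncorrected and unseen.

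The size depends on counts that the protocol does not give. Under the assumption of two unobserved abatacept non-starters, the p-value is 0.017 or 0.070 according to the set. One is enough when the result is closer to the boundary, and three are needed at about the design rates. With observed outcomes, or with non-starters in the control arm, the effect can be negligible or reversed. A reader should not conclude that the primary comparison is biased towards abatacept, since the documents do not establish a direction.

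The eligibility exclusions are a minor matter.

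**What to change.** - Define the primary set as all randomised patients, analysed in the arm allocated. Use observed RA status wherever follow-up exists, and the protocol's missing-equals-failure rule otherwise.
- Keep the mFAS, with its conditional eligibility exclusions, and the per-protocol set as sensitivity analyses.
- Delete the parenthesis that equates the mFAS with ITT.
- Replace the code-break milestone with a SAP signed before any 12-month results by arm are seen.

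**Cost.** The change is mainly wording in the protocol and SAP. Including non-starters dilutes the estimated effect slightly. They also need follow-up for RA status, which section 8.8 already asks for. Section 8.9 promises it only where possible, and section 7.4 returns withdrawn patients to routine clinics, so some effort to obtain month-24 status would be needed. No increase in the number randomised is required: 35 per arm analysed is the number on which the 80% power rests.
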